### Patient population

A total of 200 patients with AIS admitted to the emergency room are eligible for this study. The patients will be divided into two groups: One hundred will be assigned to the experimental group and 100 to the control group. This will allow the intervention to start from day 0 of hospitalization in the neurology ward.

The inclusion and exclusion criteria are listed in Table 1.

**Table 1: T1:** The inclusion and exclusion criteria.

**Inclusion Criteria**	**Exclusion Criteria**
Patients aged 50-80 years	Reperfusion treatment (intravenous thrombolysis, mechanical thrombectomy)
5 < NIHSS scores < 25	Hemorrhagic stroke on CT scan
Ischemic stroke confirmed by CT scan	5 > NIHSS scores > 25
<24 hours from onset to treatment	Fluctuating neurological deficit
Signed informed consent	Transient ischemic attack
	Other cerebral lesions: cerebral tumors, arteriovenous malformation.
	Uncontrolled blood pressure with systolic pressure < 90/60 mmHg or > 200/100 mmHg
	Difference between systolic blood pressure in the upper arms > 10 mmHg
	Ischemic events in the last 6 months (AIS, myocardial infarction and others)
	Premorbid Rankin >3
	Comorbidity with any serious diseases and life expectancy of less than 6 month

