### Intervention

The subjects will be double-masked and randomized into the experimental and control group in a 1:1 ratio, according to the predefined drawing lots.

A manual tourniquet will be placed around the upper arm, contralateral to the neurological deficit (to reduce the possible local adverse events) in the first 24 hours after the diagnosis of AIS. All patients will receive five cycles of three-minute inflation of the blood pressure cuff, followed by five minutes of reperfusion. The procedure will be performed twice daily (morning and afternoon) during the first five days of hospitalization. In the experimental group, the level of cuff inflation will be >20 mmHg above the systolic blood pressure, up to 180 mmHg. The subjects in the control group will receive cuff inflation up to 30 mmHg, which will induce sham conditioning.

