## Results

The primary outcome measure will be radiological, assessing the difference of brain infarct volume measured by CT at baseline and 180 days in the experimental group versus the control group. The CT scan will be performed at day 3-4 (or at discharge) and 180 days. The baseline infarct volume will be determined as the hypodensity image on the CT scan and measured by manual outlining. The follow-up volume at 180 days will be defined by the same method. The infarct growth will be defined as the difference between the follow-up volume and the baseline volume. The radiologist will be blinded to the clinical data, and the group examined. The same CT scan protocol will be used in both centers.

The second outcome measure will be clinical and will assess the magnitude of improvement by

1.Incidence of improvement or deterioration (not due to hemorrhage transformation) of NIHSS at 90 and 180 days compared with baseline;2.Modified Rankin Scale (mRS), Instrumental Activities of Daily Living (IADL), Activities of Daily Living (ADL), Montreal Cognitive Assessment (MoCA), Patient Health Questionnaire-9 (PHQ-9) scores at 90 days and 180 days compared to baseline;3.Tolerance and side effects of RIC;4.Recurrence of stroke or other vascular events at 180 days;5.Incidence of stroke-associated comorbidities;6.The proportion of death by any cause during 180 days.

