### Statistical analysis

The statistical analysis of the data will be conducted using SPSS 20.0 Software. Descriptive epidemiology, a correlation between risk factors and outcomes, a comparison between the two groups in terms of clinical and radiological outcomes as well as adverse effects are targeted.

Current status: at the time of the first submission of the article, 40 patients have been recruited.

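### Secondary outcome item 1 leaves out NIHSS deterioration caused by hemorrhagic transformation, so that one item misstates the total effect of conditioning if transformation rates differ between arms

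*Protocol article*

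**What the plan says.** The Results section of the protocol article lists six secondary items. Item 1 is the incidence of "improvement or deterioration (not due to hemorrhage transformation) of NIHSS at 90 and 180 days compared with baseline". The article does not say whether a patient whose worsening is put down to transformation counts as not deteriorated or is left out of the analysis.

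The other five items have no such exclusion:

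- Item 2 covers mRS, IADL, ADL, MoCA and "Patient Health Questionnaire-9 (PHQ-9) scores at 90 days and 180 days compared to baseline".
- Item 3 is "Tolerance and side effects of RIC".
- Item 4 is "Recurrence of stroke or other vascular events at 180 days".
- Item 5 is the incidence of stroke-associated comorbidities.
- Item 6 is "The proportion of death by any cause during 180 days".

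None of the six names hemorrhagic transformation as an outcome in its own right. The primary outcome, CT infarct volume, has no hemorrhage exclusion. The Abstract and Table 2 list NIHSS without the exclusion. The Statistical analysis section says that "a comparison between the two groups in terms of clinical and radiological outcomes as well as adverse effects are targeted".

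Three further facts bear on timing. Table 1 excludes patients with "Hemorrhagic stroke on CT scan". The Intervention section states: "The procedure will be performed twice daily (morning and afternoon) during the first five days of hospitalization". The scheduled CTs are at day 3-4 (or discharge) and at day 180, and Table 2 shows none at day 90.

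**The concern.** Item 1 is conditioned on the cause of a post-randomisation event. Hemorrhage on CT is screened out at entry and conditioning runs over the first five days, so the transformation in question arises after enrolment, during or after treatment. The Introduction attributes to RIC effects on the cerebral vasculature and on inflammation, and the trial aims to shrink the infarct. An effect on bleeding into the infarct, in either direction, cannot be ruled out on that rationale. The article gives no reason to assume equal rates.

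If RIC raises transformation, item 1 does not show the resulting neurological worsening. If RIC lowers it, item 1 discards part of a real benefit. The trial states safety as an aim alongside efficacy, so both directions matter.

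The exclusion also needs a causal judgement. Someone must decide that a worsening seen at day 90 or day 180 was due to transformation, with no scheduled CT at day 90 and a first CT that may precede the end of the five-day course.

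**Working it through.** The article states no event rate, effect size or power for any outcome, so there is no figure to reproduce. The only input taken from it is the group size: 100 per arm (Patient population section). All rates below are assumptions.

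**Notation.** Let *d* be the proportion with deterioration from other causes, and *h0* and *h1* the proportions with transformation-related deterioration under sham and RIC. The two kinds are treated as mutually exclusive, and *d* is the same in both arms. Differences are RIC minus sham.

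- All-cause difference: (d + h1) - (d + h0) = h1 - h0.
- Excluded cases counted as non-events: d - d = 0.
- Excluded cases removed from the denominator: d/(1 - h1) - d/(1 - h0).

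**Main illustration: d = 10%, h0 = 3%, h1 = 8%.**

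- All-cause: 18% - 13% = +5 points. SE = sqrt(0.13 × 0.87/100 + 0.18 × 0.82/100) = 0.051, so the 95% CI is 0.05 ± 1.96 × 0.051, about -5 to +15 points.
- Non-events: 10% - 10% = 0.
- Removed: 10/92 - 10/97 = 10.9% - 10.3% = about +0.6 points.

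**Range of assumed rates.** The last column runs over d = 10% to 20%.

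| h0 (sham) | h1 (RIC) | All-cause difference | Non-events | Removed |
|---|---|---|---|---|
| 3% | 3% | 0 | 0 | 0 |
| 3% | 6% | +3.0 | 0 | +0.3 to +0.7 |
| 5% | 10% | +5.0 | 0 | +0.6 to +1.2 |
| 5% | 2.5% | -2.5 | 0 | -0.3 to -0.5 |

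Under the non-event reading, the whole between-arm difference due to transformation disappears. Under the removal reading, a small residue with the same sign remains.

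**Equal transformation rates.** If h0 = h1 = h but other-cause deterioration differs between arms (d0 and d1), the non-event reading gives d1 - d0, which equals the all-cause difference. The removal reading gives (d1 - d0)/(1 - h). At h = 3% this multiplies the difference by 1/0.97, or about 1.03.

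**The case against.** The strongest reply is that the exclusion touches one of six secondary items. A disabling transformation would still register in mRS, ADL and IADL, and a fatal one in all-cause death. Adverse effects are to be compared between groups. The trial is described as double-blind with a blinded radiologist, so attribution of cause need not favour an arm. Most of this stands, and it limits the point to item 1. It does not repair item 1: even perfect, blinded attribution removes a possible effect of treatment from the count. The other items do not isolate the event either. The disability scores record the consequence but not the cause, all-cause death catches only fatal cases, and item 3 captures transformation only if it is classed as a side effect of conditioning.

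A reader might infer more than the article supports:

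- **That the whole efficacy and safety comparison is biased, or the main clinical outcome compromised.** The primary outcome and items 2 to 6 are unrestricted, and the article ranks no clinical outcome as the main one.
- **That randomisation is broken.** If excluded cases count as non-events, item 1 is a cause-specific endpoint in all randomised patients: incomplete, but still a randomised comparison. Only removing those patients departs from the randomised groups, and the article does not say which is meant.
- **That RIC causes transformation.** The article does not say so and gives no rate. Even at the assumed 13% versus 18%, the interval includes zero.
- **That deaths drop out of item 1.** The article does not say this. Handling of deaths in a score-based outcome may be left to the full protocol or analysis plan, and all-cause death is item 6.

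**Conclusion.** The point holds for item 1 alone. The exclusion is a stated rule, not a detail that a condensed article has left out. It misstates the total effect of RIC on neurological deterioration whenever transformation rates differ between arms. Over the assumed rates in the table, an all-cause difference of -2.5 to +5 points becomes 0 under the non-event reading, or about -0.5 to +1.2 points under removal. These figures rest on assumed rates, mutually exclusive causes and equal other-cause deterioration in the two arms. With equal transformation rates and excluded cases counted as non-events, the difference is not distorted. Bias is therefore conditional, and neither its presence nor its direction can be established from the article.

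**What to change.** In item 1, delete the bracketed exclusion so that the item counts NIHSS deterioration from any cause in all randomised patients. Keep the version without transformation-related cases as a supportive analysis only, and state whether those cases count as non-events or are removed.

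Add hemorrhagic transformation, by arm, as a named safety outcome. Read it from the planned day 3-4 (or discharge) and day-180 CTs plus any clinically prompted scans. The day 3-4 scan alone is not enough, because conditioning continues to day five and the next scheduled CT is at day 180. The report should acknowledge that scheduled scans may miss some events.

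The cost is a change of wording and an extra reading of scans already planned or taken, with no new visit or scheduled scan. The deterioration rate may look slightly worse in both arms. The article reports 40 of the planned 200 patients recruited at first submission, so the change should be dated and made without sight of outcomes by arm.

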### Statistical analysis

The statistical analysis of the data will be conducted using SPSS 20.0 Software. Descriptive epidemiology, a correlation between risk factors and outcomes, a comparison between the two groups in terms of clinical and radiological outcomes as well as adverse effects are targeted.

Current status: at the time of the first submission of the article, 40 patients have been recruited.

## Discussion

To our knowledge, this is the first clinical trial to investigate the effect of RIC after a stroke by measuring the ischemic volume on the CT scan.

The primary outcome measure in our study will be radiological, showing the difference in brain infarct size volume between the experimental group and the control group. In the STAIR Group 2016 (Stroke Treatment Academic Industry Roundtable [4]), the infarct volume has been chosen as the radiological objective outcome, being linked to the clinical outcome [5].

The clinical outcome measure will be investigated as a second target using multiple validated scales: NIHSS, Rankin, Barthel, IADL, ADL. All these reflect the quality of life of a stroke survivor. Also, impaired scores are associated with poorer medical health, increasing medical costs. We will also investigate the cognitive status (MoCA test) and depression (PHQ-9 test) comparing the two groups at baseline, at 90 days, and 180 days.

Our study differs in some respects compared to previous ones. Firstly, it is a multicentre study, including patients from 2 hospitals. Secondly, all the patients will have an ischemic stroke confirmed on the CT scan. Previous studies assessed the brain infarct volume on MRI (REPOST study [6], RESCUE study [7], RECAST study [8], Hougaard’s study [9], Meng’s study [10], Mi’s study [11], Wang’s study [12]). Thirdly, we will include moderate and severe stroke patients (NIHSS= 5-25). Previous studies included either mild-moderate (NIHSS= 0-15) [10,13] or any stroke severity [9]. Fourthly, we will include all ischemic stroke subtypes, according to the TOAST classification. Fifthly, we will measure the final infarct volume at 180 days (6 months). Previous studies measured the final infarct volume at 24 hours [7, 9] or day 4 [6]. Finally, there are different types of RIC procedures in the previous studies: sites of limb conditioning: arm, leg, both arms, both legs; cycles and duration of inflation/deflation; timing of RIC; frequency: once or repeated /day.

## Conclusion

Remote ischemic conditioning represents a promising therapy, inexpensive, and well-tolerated, which might be neuroprotective. Provided that remote ischemic conditioning shows good results in terms of efficiency, it could be easily implanted as a routine procedure in prehospital, emergency room, all hospitals, or even intensive care units.
